### Intervention

All the subjects, including both the normoxia (control) and the hypoxia groups, will undergo four weeks of aerobic exercise training and dieting (eating a balanced diet). In addition, the normoxia group will sleep in normal conditions while the hypoxia group will sleep in a normobaric hypoxic chamber every night. All the measurements will be conducted two days prior to, and post-intervention, and repeated two months later after the intervention (two months follow-up). Fasting blood samples will be collected in the morning of the testing day. In order to maximize the compliance and avoid the occurrence of any accident the intervention will be closely supervised by a physician, a dietitian, and an exercise physiologist.

### Exercise training

The same aerobic exercise training will be applied to both the normoxia and the hypoxia groups. Participants will exercise for six days per week, twice daily, for one hour per session. The intensity of the exercise will be estimated using the Metabolic Equivalent of Task (MET) score. MET, the unit of energy expenditure, will be obtained by dividing oxygen uptake values (ml · kg^-1^ · min^-1^) by 3.5 (1 MET is defined as resting metabolic rate that is 3.5 ml · kg - 1 · min - 1). VO_2_ will be measured using Cosmed K4b2 Portable Metabolic Measurement System (Cosmed, S.r.l., Rome, Italy) according to the manufacturer’s instructions.To promote participants’ interest, the exercise training will consist of three different activities including swimming (intensity: 6 MET), aerobic exercise (intensity: 7.5 MET), and basketball (intensity: 6 MET).

### Diet modification

All participants will receive well-defined and balanced daily meals during the four-week intervention. Dietary recommendations will be individualized based on the individual’s basal metabolic rate and will range from 1,600 to 2,000 kcal/day. The basal metabolic rate will be calculated using the Mifflin equation [28]. The caloric intake will be calculated based on the Chinese food chart. Each day, three well-balanced meals will be provided with the following calorie allocations: breakfast 35%, lunch 40%, and dinner 25%. Each meal comprises 30% protein, 20% fat, and 50% carbohydrate by energy. Animal and vegetable oil and starch-rich food will be minimized, while the intake of vegetables, fruits, bean products, rabbit meat, beef, pork, and cellulose will be increased. This prescribed diet includes pivotal nutrients such as vitamins, minerals, essential amino acids, fiber, and polyunsaturated fatty acids.

### Hypoxia exposure

To test the hypothesis that hypoxia exposure would ameliorate the compensatory increase in appetite elicited by exercise and diet, the experimental group (hypoxia group) will sleep in a normobaric hypoxia environmental chamber every night during the four- week intervention. The advantage of using an environmental chamber compared to real altitude situations is that the effects of hypoxia can be isolated from the influence of other confounding factors present in a real altitude situation, such as the influence of temperature, humidity, and physical activity levels. The normobaric hypoxia will be designed to mimic an altitude of 2700 m. We will use the large hypoxic training system (Low Oxygen System, Dubai, Germany)) of the hypoxia test laboratory of Shanghai Oriental Oasis Training Base to simulate a hypoxic environment (14.7% O2; approximately 2700 m). After a one-day hypoxia acclimation period, participants of the hypoxia group will sleep in the hypoxia training laboratory for 10 hours every night (from 21:00 to approximately 7:00 the next day), seven times per week, for four weeks.

### Attrition and compliance

Due to the voluntary nature of the enrollment of the summer weight loss camp, attrition rates will be very low. In a pilot trial involving 50 overweight male Chinese adolescents, 47 children completed a four-week diet and exercise intervention, and only three children (6%) dropped out of the study due to loss of interest. Considering the addition of a two-month follow-up, we expect a higher attrition rate (15%) in this study. Our recruitment plan was made based on this consideration.

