### Sample size estimation

Sample size estimation in this RCT is based on the expected fat loss following four weeks of hypoxia exposure plus exercise and dieting. The data of our preliminary experiment showed that the means of fat percentage decrease in the normoxia and hypoxia groups were 3.1 and 6.0% respectively, and the standard deviation of the change was about 3%. It is estimated that a sample size of 17 participants per group will be required to observe a similar result with a power of 80%. Considering a 15% dropout and exit rate, we will recruit 40 subjects with 20 in each group.

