### Data management and statistical analysis

Data generated in the study will be collected and summarized using mean (standard deviation) values. Group differences in demographical and clinical characteristics at baseline will be tested using a two-sample t-test for quantitative data and chi-square test for qualitative data. Repeated measures analysis of variance (RM ANOVA) will be used to analyze the main effect of treatment and potential time-by-treatment interactions. For these analyses, parametric assumptions of the normality and homoscedasticity will be checked using standard tests and graphical methods. If those assumptions are violated, data transformation and non-parametric procedures will be considered sequentially. Multivariate regression analysis will be performed to analyze the relationship between changes in body composition, appetite score, and gastrointestinal hormones following intervention and during follow-up. Multiple models will be developed and tested for different sets of outcome measures and regressor variables. All statistical analyses will be performed using the Statistical Package for the Social Sciences (SPSS, Inc., Chicago, Illinois, United States) for Windows version 18.0, and a significance level of 0.05 will be used.

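### RM ANOVA, read as one three-visit model, would leave out about 3 to 4 of 40 children with observed 4-week data because they miss the 2-month visit

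*Protocol article*

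**What the plan says.** Data management and statistical analysis: "Repeated measures analysis of variance (RM ANOVA) will be used to analyze the main effect of treatment", together with possible time-by-treatment interactions, in SPSS 18, and "a significance level of 0.05 will be used". The section covers assumption checks, transformation and non-parametric fallbacks. No other between-group efficacy method is named.

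The Abstract and Outcome assessments place the measurements at baseline, after the 4-week intervention and at 2 months.

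Attrition and compliance reports that 3 of 50 children (6%) left a 4-week diet and exercise pilot. It continues: "Considering the addition of a two-month follow-up, we expect a higher attrition rate (15%) in this study".

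Sample size estimation is "based on the expected fat loss following four weeks of hypoxia exposure plus exercise and dieting". Its inputs are that "the means of fat percentage decrease in the normoxia and hypoxia groups were 3.1 and 6.0% respectively" and that "the standard deviation of the change was about 3" (per cent). It concludes that "a sample size of 17 participants per group will be required to observe a similar result with a power of 80" (per cent), and then: "Considering a 15% dropout and exit rate, we will recruit 40 subjects with 20 in each group". Recruiting 20 instead of 17 per group is the only response to attrition that the article states.

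**The concern.** Classical RM ANOVA needs a full set of outcomes for each subject. A child with DXA at baseline and 4 weeks but none at 2 months drops out of a three-visit model, and the observed 4-week value goes too. The protocol itself predicts such children, since it attributes the rise from 6% to 15% to the added follow-up.

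The data left out belong to the 4-week change for which the trial is sized. Recruiting more children restores the numbers. It does not restore the randomised comparison, because the 4-week effect would then be estimated among children selected by something that happens after randomisation: coming back two months later. If that selection works differently in the two arms, the estimate shifts. Differential return is conceivable, because children know whether they sleep in the chamber and the second hypothesis in the Background expects less rebound in the hypoxia group.

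**Working it through.** **Inputs.** Difference 6.0 - 3.1 = 2.9 points; SD of change 3 points; power 80%; 17 per group, inflated to 20 for 15% dropout (Sample size estimation). Alpha 0.05 (Data management and statistical analysis); sidedness is not stated, so two-sided is assumed. Pilot attrition 3/50 = 6% and expected attrition 15% (Attrition and compliance).

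**1. The plan's own figure.** n per group = 2 × [SD × (1.960 + 0.842) / difference]² = 2 × (3 × 2.802 / 2.9)² = 16.8, so 17. Then 17 / 0.85 = 20 per group, 40 in total. Both stated figures reproduce. The t-based calculation gives 17.8, so 18.

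**2. Children affected.** Assumption: 6% missing at 4 weeks (the pilot rate, from boys on diet and exercise) and 15% missing by 2 months.
- With 4-week data: 40 × 0.94 = 37.6 (18.8 per arm).
- With all visits: 40 × 0.85 = 34 (17 per arm).
- Observed at 4 weeks but left out: 37.6 - 34 = 3.6.
- Range: 0 if all the attrition falls before week 4; 40 × 0.15 = 6 if all of it falls after.

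**3. Power for the 4-week contrast** (difference 2.9, SD 3, two-sided 0.05).

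| Per arm | Normal approximation | t-test |
|---|---|---|
| 17 (all visits) | 80.5% | 78.0% |
| 18.8 (all observed 4-week data) | 84.2% | 82.2% |
| 20 (no loss before week 4) | 86.4% | 84.6% |

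With the assumed rates the cost is about 4 points. That 78.0% lies below 80% reflects t-test against normal sizing, not attrition.

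**4. Possible bias.** Assumption, for illustration only: hypoxia-arm children lost after week 4 did 3 points worse at 4 weeks than those who returned, and control losses are typical. Among hypoxia children with 4-week data, the share lost later is 0.09 / 0.94 = 0.096. The completers' mean then exceeds the mean of all observed values by 0.096 × 3 = 0.29 points, and 0.29 / 2.9 = 10%.

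**5. Simulation of the mechanism.** True difference 2.9, 20 per arm, the missingness rates of step 2, and 6,000 runs per setting. The log-odds of returning at 2 months depend on 4-week response with slope +1 or -1 per SD, or not at all.

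| Return depends on response | Returners only: mean estimate (power) | All observed 4-week data |
|---|---|---|
| In neither arm | 2.92 (78%) | 2.92 (81%) |
| Equally in both arms | 2.90 (80%) | 2.89 (82%) |
| Control arm only | 2.65 (71%) | 2.90 (82%) |
| Hypoxia arm only | 3.14 (85%) | 2.88 (81%) |
| Opposite directions by arm | 2.38 (64%) | 2.91 (82%) |

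The returners-only estimate moves only when return relates to response differently by arm, and it can move either way.

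**The case against.** The strongest reply is that the article does not say one model spans all three visits, that analysis is complete-case, or that nothing is imputed. The Design section states the short-term and long-term effects as separate aims, so separate two-visit models would fit the text. A condensed article may also leave analysis sets and missing-data handling to a fuller document. This stands as a limit on certainty, and the absence of such detail is not the point here. What remains is a stated method set against a stated expectation of late losses. One three-visit model is the natural reading of RM ANOVA with a time-by-treatment term, and nothing in the text offsets its consequence.

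Several stronger readings are tempting, and the documents do not support them:
- **That the 4-week contrast is the declared primary comparison.** The article names body composition as primary and does not rank the time points. The weight given to 4 weeks comes from the sample-size basis.
- **That sizing on 17 per group shows deletion was intended, or that the trial is underpowered.** Going from 17 to 20 is an ordinary dropout allowance, and it leaves power near the planned 80%.
- **That the full 15% applies in the bias illustration, giving 0.15 × 3 = 0.45 points (16% of 2.9).** With 6% already missing at 4 weeks, this counts children who have no 4-week value under any method. It would apply only if every loss came after week 4.
- **That chamber intolerance drives the selection.** A child who cannot tolerate the chamber would mostly leave before a 4-week value exists. The article reports loss of interest as the reason for pilot dropout, and good tolerance in the 2013 pilot (Trial status).

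**Conclusion.** The point holds in a limited form. On the natural reading of the analysis section, about 3 to 4 of 40 children (range 0 to 6) would have observed 4-week data left out of the contrast behind the sample size. The cost in power is about 4 points and leaves roughly the planned level, so this is a matter of selection rather than size. Bias is possible but not shown. It requires return at 2 months to relate to response differently by arm, and the documents give no data on that; the 0.29 points (10% of 2.9) is an illustration under an unsupported one-arm, 3-point deficit. The conclusion rests on three inferences: a single three-visit complete-case model, the pilot's 6% carrying over to week 4, and the 4-week change being the contrast of most weight. Because a better-suited method costs almost nothing, the change should be made.

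**What to change.** Make the main analysis a likelihood-based mixed model for repeated measures (SPSS MIXED) on all randomised children in their assigned groups. Use the 4-week and 2-month values as outcomes, the baseline value as covariate, terms for visit, arm and arm-by-visit, and an unstructured covariance. Each child with at least one post-baseline value then contributes. State that the 4-week contrast does not require attendance at 2 months. Keep the completers-only RM ANOVA as a sensitivity analysis.

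The cost is revised wording and different syntax, with no extra visits, children or measurements. The model relies on data being missing at random given the observed values, and the plan should say so.

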### Outcome assessments

Baseline assessments will be conducted two days before the onset of the four-week intervention. Post-intervention and two month follow-up assessments will be conducted two days and two months after completion of the intervention, respectively. The primary outcome of the study will be body composition and the secondary outcome measures will include appetite score and blood levels of gastrointestinal hormones including leptin, ghrelin, PYY, CCK and GLP-1, as well as circulating levels of IL-6. All the assessments will be performed in the laboratory of exercise physiology at the Shanghai University of Sport.

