**Methods/Design:**

In this randomized parallel group controlled clinical trial, 40 obese adolescents (20 boys and 20 girls, 11 to 15-years-old), will be recruited from a summer weight loss camp at the Shanghai University of Sport, China. Participants will be stratified by gender and randomly assigned to either the control group or the hypoxia group. During the four-week intervention period, both groups will exercise and eat a balanced diet. Additionally, the control group will sleep in normal conditions, while the hypoxia group will sleep in a normobaric hypoxia chamber (sleep high and train low). The primary outcome will be body composition and the main secondary outcomes will be the circulating levels of appetite regulatory gastrointestinal hormones. All the outcome measures will be assessed at baseline, after the four-week intervention, and at two months follow-up.

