### Aims

The aims of this randomized controlled trial (RCT) are to evaluate the effectiveness of intermittent hypoxia and exercise, in combination with a balanced diet, on inducing short- and longterm fat loss in Chinese children and adolescents, and to determine the molecular mechanisms behind the benefits of hypoxia in enhancing weight loss.

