## Methods/Design

### Design

This study is a randomized controlled clinical trial with two parallel arms involving 40 obese adolescents. To assess the effectiveness of four weeks of intermittent hypoxia added to a traditional exercise and diet intervention on inducing short (after the four-week intervention) and longterm (at two months follow-up) weight loss in obese adolescents, we will recruit 20 adolescent boys and 20 adolescent girls (aged 11 to 15 years) from our summer weight loss camp. They will be stratified according to gender and randomly assigned to two groups: the control group who will exercise, eat a balanced diet, and sleep in a normobaric condition, and the hypoxia group, who will exercise, eat a balanced diet, and sleep in normobaric hypoxia chambers (‘sleep high and train low’). Outcome assessment and data analysis will be performed by trained professionals who will be blinded to the group assignment of subjects. The flow of participants through the trial is shown in Figure 1.

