### Primary outcome

#### Body composition

Body mass and height will be measured using a digital scale (Yaohua Weighing System Co., Shanghai, China) and a wall-mounted stadiometer (TANITA, Tokyo, Japan), respectively. Body composition and fat distribution will be measured using dual energy X-ray absorptiometry (DXA) (GE Lunar Prodigy, Madison, Wisconsin, United States)). The software (ENCORE, version 10.50.086, GE, Madison, Wisconsin, United States)) will be used to analyze total lean mass (TLM), total fat mass (TFM), total body fat percentage (%TBF), android fat percentage (%AF), and gynoid fat percentage (%GF).

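### The primary outcome is a family of body-composition variables with no decisive variable, visit or effect named, while the sample size and its 80% power cover one test of fat percentage change at four weeks

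*Protocol article*

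**What the plan says.** The Outcome assessments section defines the primary outcome as a domain: "The primary outcome of the study will be body composition". The abstract does the same. The Body composition subsection, under the Primary outcome heading, covers body mass and height and then the DXA variables to be analysed: "total lean mass (TLM), total fat mass (TFM), total body fat percentage (%TBF), android fat percentage (%AF), and gynoid fat percentage (%GF"). None of these is ranked above the others.

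On timing, the abstract states: "All the outcome measures will be assessed at baseline, after the four-week intervention, and at two months follow-up". The Design section makes both post-baseline times objectives: "short (after the four-week intervention) and longterm (at two months follow-up) weight loss in obese adolescents". Neither visit is called primary.

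The target also shifts between sections. The title and hypotheses speak of weight loss. The Aims speak of "inducing short- and longterm fat loss in Chinese children and adolescents". The Sample size estimation section is narrower: "Sample size estimation in this RCT is based on the expected fat loss following four weeks of hypoxia exposure plus exercise and dieting". It uses pilot decreases in fat percentage of 3.1% and 6.0%, with an SD of change of about 3%.

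The Data management and statistical analysis section specifies repeated-measures ANOVA, looking at the treatment main effect and the time-by-treatment interaction. For all analyses, "a significance level of 0.05 will be used".

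**The concern.** The sample size implies one endpoint at one time, but the outcome section names a family. The document does not say which variable, visit or ANOVA effect answers the trial's question. A positive conclusion could therefore rest on whichever member of the family turned out favourable, and the stated power would not apply to most of the candidates. The two-month objective has no stated power at all.

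Direction matters too. Lower values of the fat measures serve the stated aim. A fall in total lean mass would also be an effect on body composition and on weight, but it is not fat loss. An unranked family does not say which of these results would count as success.

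**Working it through.** **Inputs from the protocol article.** Difference 6.0 − 3.1 = 2.9; SD of change 3; 80% power; 17 per group; 15% dropout; 20 per group and 40 in total (Sample size estimation). Significance level 0.05 (Data management and statistical analysis). Sidedness is not stated.

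**Step 1: reproduce the stated sample size.** Two-sided 0.05, normal approximation:

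n = 2 × SD² × (1.960 + 0.842)² / difference² = 2 × 9 × 7.85 / 8.41 ≈ 16.8, so 17 per group. With 15% dropout, 17 / 0.85 = 20 per group.

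Both stated figures are reproduced. Power at 17 per group is 80.5% by normal approximation and 78.0% by the t distribution, which would ask for 18. A one-sided test would need only 14, so the two-sided reading fits. The 17 is the size for one test of one variable at one time.

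**Step 2: count the tests available.** Five DXA variables are listed; body mass would be a sixth and is left out of the count. Repeated-measures ANOVA analyses the visits together and gives two effects per variable. If one effect per variable is used there are 5 tests; if either effect may be cited there are 5 × 2 = 10. With three measurement occasions, neither the main effect nor the overall interaction is by itself the four-week contrast for which the trial was sized.

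**Step 3: chance of at least one false positive, each test at 0.05.** Under independence this is 1 − 0.95^k: 22.6% for k = 5 and 40.1% for k = 10. For correlated tests it was simulated with equally correlated normal statistics (400,000 draws), treating each test as two-sided normal. That is a simplification for the interaction test. The correlations are assumptions, because the document gives none.

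| Assumed correlation | 5 tests | 10 tests |
|---|---|---|
| 0 (independent) | 22.6% | 40.1% |
| 0.5 | 18% | 29% |
| 0.7 | 15% | 21% |
| 0.9 | 10% | 13% |

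**Step 4: cost of keeping all five variables primary.** Bonferroni level 0.05 / 5 = 0.01, assuming the same standardised effect (2.9 / 3) for each variable:

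| | Level 0.05 | Level 0.01 |
|---|---|---|
| Power at 17 per group, normal approximation | 80% | 60% |
| Power at 17 per group, t-based | 78% | 54% |
| n per group for 80% power, normal approximation | 17 | 25 |
| n per group for 80% power, t-based | 18 | 27 |

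After 15% dropout, 27 becomes 27 / 0.85 ≈ 31.8, so 32 per group against the 20 planned.

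**The case against.** The best defence has four parts.

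- **Measurement list.** The Body composition subsection describes what is measured. It also covers height, which nobody would take as an endpoint, so the DXA list may be no more than scanner output. The sample size section shows that fat percentage was the planning variable. This is a fair reading of intent, but the outcome section does not state it, and the list stands under the primary-outcome heading.
- **Test structure.** A reader might infer separate 0.05 tests of each variable at each visit. The document does not say that; it specifies repeated-measures ANOVA. The count of ten comes only from two effects per variable with neither named as decisive, and it is an upper count of what is available, not a list of planned tests.
- **Multiplicity rules may lie elsewhere.** A reader might infer that the trial has no controlled primary test. The article does not support that. It is silent on adjustment and ordering, and an analysis plan that is not shown could supply both. What stands is a mismatch within the article: it gives the primary outcome its own section, fixes it as a family, and sizes the trial on one member.
- **Magnitude.** A reader might take 40% as the error rate, or set 54% power beside the stated 80%. Neither is right. Fat mass, lean mass and fat percentage are linked by construction, and the visits are repeated measures on the same people, so independence is implausible. The 54% is t-based and belongs beside 78%.

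**Conclusion.** The point holds in this limited form. The stated primary outcome is wider than the endpoint for which the trial was sized, and the protocol as shown does not say which variable, time or model effect is decisive. At assumed correlations of 0.9 to 0.5, the chance of at least one false positive is about 10% to 18% for five tests and 13% to 29% for ten. In every case shown this is at least about twice the nominal 5%. The independence figures of 23% and 40% are outer limits, not expectations.

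The sample size arithmetic is correct for its one test. The conclusion assumes a two-sided test and no multiplicity rule in documents not shown. It also leaves one uncertainty open: the sample size section says only that fat percentage decreased. Total body fat percentage in percentage points is the closest listed variable, but a relative decrease in fat cannot be excluded from the text.

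**What to change.** 1. Confirm that the fat percentage decrease behind the sample size is change in total body fat percentage, in percentage points.
2. If so, name one primary endpoint and one decisive contrast: the between-group difference in change in total body fat percentage from baseline to four weeks, at two-sided 0.05. State that this contrast, taken from the repeated-measures model or an equivalent baseline-adjusted analysis, decides the trial.
3. Test total body fat percentage at two months only if the primary contrast is significant. Placing four weeks first follows the sample size basis. The investigators should confirm that order, since the longer-term effect is also an objective.
4. Report total fat mass, total lean mass, android and gynoid fat percentage and body mass as secondary, with confidence intervals. Read lean mass as a check that weight loss is fat loss.

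The cost is a change of wording in the outcome and analysis sections and a matching registry entry. The planned 40 participants stand. The downside is that the other body-composition results lose confirmatory status.
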